## Abstract

**Background:**

Schizophrenia is a persistent and debilitating mental illness, and its prognosis depends largely on supportive care and systematic treatment. In developing countries like China, families constitute the major caregiving force for schizophrenia and are faced with many challenges, such as lack of knowledge, skills, and resources. The approach to support family caregiving in an accessible, affordable, feasible, and cost-effective way remains unclear. The wide-spread use of WeChat provides a promising and cost-effective medium for support.

**Objective:**

We aim to present a protocol for assessing a WeChat-based integrative family intervention (WIFI) to support family caregiving for schizophrenia.

**Methods:**

We will develop a WIFI program that includes the following three core components: (1) psychoeducation (WeChat official account), (2) peer support (WeChat chat group), and (3) professional support (WeChat video chat). A rigorous stepped-wedge cluster randomized trial will be used to evaluate the implementation, effectiveness, and cost of the WIFI program. The WIFI program will be implemented in 12 communities affiliated with Changsha Psychiatric Hospital through the free medicine delivery process in the 686 Program. The 12 communities will be randomized to one of four fixed sequences every 2 months during an 8-month intervention period in four clusters of three communities each. Outcomes will be assessed for both family caregivers and people with schizophrenia. Family caregivers will be assessed for their knowledge and skills about caregiving, social support, coping, perceived stigma, caregiver burden, family functioning, positive feelings, and psychological distress. People with schizophrenia will be assessed for their symptoms, functioning, quality of life, recovery, and rehospitalization. Cost data, such as intervention costs, health care utilization costs, and costs associated with lost productivity, will be collected. Moreover, we will collect process data, including fidelity and quality of program implementation, as well as user attitude data. Treatment effects will be estimated using generalized linear maximum likelihood mixed modeling with clusters as a random effect and time as a fixed effect. Cost-effectiveness analysis will be performed from the societal perspective using incremental cost-effectiveness ratios. Qualitative analysis will use the grounded theory approach and immersion-crystallization process.

**Results:**

The study was funded in August 2018 and approved by the institutional review board on January 15, 2019. Preliminary baseline data collection was conducted in May 2019 and completed in September 2019. The WIFI program is expected to start in September 2020.

**Conclusions:**

This is the first study to assess a WeChat-based mHealth intervention to support family caregiving for schizophrenia in China. The innovative study will contribute to the development of a more cost-effective and evidence-based family management model in the community for people with schizophrenia, and the approach could potentially be integrated into national policy and adapted for use in other populations.

**Trial Registration:**

ClinicalTrials.gov NCT04393896; https://clinicaltrials.gov/ct2/show/NCT04393896.

**International Registered Report Identifier (IRRID):**

PRR1-10.2196/18538

## Introduction

### Schizophrenia and Family Caregiving

Globally, schizophrenia is a debilitating persistent psychiatric disorder affecting over 21 million people [1,2], and there is a 60% increase in premature deaths among people living with schizophrenia compared with the general population [3]. The most recent global burden of disease study in 2016 showed that schizophrenia contributes 13.4 million years of life lived with disability to the burden of disease globally [2]. The prognosis of schizophrenia depends largely on integrated mental health and social care services in community-based settings, which has been listed by the World Health Organization (WHO) as one of the four major objectives in its Mental Health Action Plan 2013-2020 [3]. Among the multiple initiatives proposed by the WHO [3], strengthening the active involvement and support of family caregivers in caring for people living with schizophrenia stands out as the most sustainable and cost-effective solution for addressing the worldwide treatment gap in resource-poor settings. Recent years have seen a global shift in the responsibility of care from the hospital setting to families [4], such that the economic value of informal family caregiving now greatly exceeds spending through formal health care systems. Recently, the Chinese government recognized the value of family caregiving by instituting the Reward Policy (described below) to support family caregivers financially [5]; however, this policy is an exception globally [6].

### The Reward Policy and Challenges

In China, there are over 7.16 million people living with schizophrenia [7], and over 90% of them live with and depend on their families for care [8]. Family caregiving often requires a range of support that extends across physical, psychological, emotional, social, and financial domains [9]. The essential roles of family caregivers in the care of schizophrenia have been increasingly recognized in China’s mental health policy. In 2016, the Chinese government instituted a Reward Policy to encourage family involvement in the care of people with serious mental illness. According to the Reward Policy, a monthly subsidy equal to the local poverty line allowance (currently at least RMB 200 or US $28.6) is paid to each family based on good management and care of the family member with serious mental illness, including schizophrenia [5,10].

Three years after its implementation, the Reward Policy has helped alleviate the financial burden for caregiving families. However, family caregivers are still faced with other challenges during the process of caregiving, such as insufficient knowledge and skills in providing appropriate care to people living with schizophrenia, social isolation due to stigma, stress from caregiving, family conflict on task-sharing, and lack of self-care due to overwhelming caregiving responsibilities [4,11,12]. As a result, family caregivers experience a considerable level of burden that not only detrimentally impacts their own health and well-being, but also leads to poor prognosis in people living with schizophrenia owing to impaired quality of care. These challenges have stimulated a focus beyond simply identifying caregiver burden to also developing effective family interventions to reduce this burden and improve care [13].

### Family Intervention Programs

To date, several family intervention programs have been developed and tested, with the following three elements identified as most promising and feasible: (1) psychoeducation for families to increase knowledge about schizophrenia and strengthen related caregiving skills; (2) peer-support for both family caregivers and people living with schizophrenia where they can share experiences and feelings, exchange information, and provide mutual emotional support; and (3) professional support to family caregivers that troubleshoots specific problems and provides private targeted guidance to address specific needs [13-18]. Thus far, integrative application of all three intervention components has been limited in China owing to their low accessibility and high cost, and evidence on their combined use and effectiveness to support family caregivers and people living with schizophrenia is lacking. An innovative, affordable, and cost-effective platform that integrates all three of these intervention components thus represents a pressing need in the scientific literature and for the national health care policy.

### WeChat Use in China

WeChat is the most common social media platform in China, with over 1 billion monthly active users of all ages [19]. About 93% of urban users log into WeChat every day [20]. WeChat features diverse platforms, such as moments, chat group, and WeChat official account (WOA), and boasts of multiple powerful functions including voice and text messaging, voice and video calls, photo sharing, payment, and games. Owing to its wide range of platforms and functions, WeChat has been dubbed China’s “app for everything” and has been characterized as “4A” (anybody, anytime, anywhere, and anything) [21,22]. The seamless integration of WeChat into every aspect of human life makes it a promising and cost-effective medium for health intervention delivery. A growing number of WeChat-based health intervention programs have been developed for patients with various health conditions, with robust evidence showing their acceptability, feasibility, and efficacy [23-27]. Specifically, WeChat-based health interventions have been found to cost less, improve treatment adherence, have fewer complications, increase rates of follow-up, require less intervention time, and improve patient satisfaction [23-27]. Thus, we hypothesize that a WeChat-based Integrative Family Intervention (WIFI) program that includes the three elements noted above (psychoeducation, peer support, and professional support) will be an accessible and cost-effective approach to improve the outcomes of both people living with schizophrenia and family caregivers.

### Theoretical Framework for the Proposed Study

The theoretical mechanisms underlying the proposed study are psychoeducation, peer support, and professional support (Figure 1). There is empirical evidence that each of these mechanisms promotes the expected outcomes examined. Psychoeducation is central to the proposed study because it directly increases knowledge about schizophrenia and caregiving and indirectly works through the actions of peers and professionals in the provision of support. More specifically, there is considerable evidence that psychoeducation has been widely employed with caregivers and with people living with schizophrenia to yield a range of positive effects. For example, with caregivers, psychoeducation has been shown to increase knowledge and skills [28], improve social support [29] and coping [30,31], improve family functioning [32], decrease stigma [28] as well as family burden [33-35], promote positive feelings and decrease emotional distress [34-36], and reduce the cost of care [37]. Furthermore, for people living with schizophrenia, psychoeducation has been shown to decrease symptoms, improve functioning, enhance quality of life, increase recovery, decrease hospitalizations, and reduce health care costs [15,38-40]. Importantly, psychoeducation also yields positive effects for caregivers and people living with schizophrenia when delivered through peer support and professional support [18,41-43].

**Figure 1 figure1:**
[figure not shown]
Theoretical framework of the proposed study. PLS: people living with schizophrenia.

Consistent with the literature, three components are included in the WIFI program to provide education and support to families (psychoeducation, peer support, and professional support) (Figure 1). WeChat will provide access for caregivers and people living with schizophrenia to each of these intervention components. Psychoeducation and support will increase knowledge and skills, as well as social support (peer and professional) and coping to reduce perceived stigma and caregiver burden. In addition, these components are expected to enhance family functioning and positive feelings, such that emotional distress will be reduced. Finally, these effects are hypothesized to reduce caregiving costs. For people living with schizophrenia, these components are expected to enhance the overall quality of care in the community, which is hypothesized to reduce symptoms in people living with schizophrenia and enhance functioning, increase quality of life and recovery, and decrease rehospitalization, thus reducing overall health care costs.

This paper describes the protocol of a study designed to assess the impact of a WIFI program fully aligned with the Reward Policy for families caring for people living with schizophrenia compared with the Reward Policy alone. The specific aims are as follows: (1) compare the effects of the WIFI program plus the Reward Policy with the Reward Policy alone on caregiving and the health outcomes of family caregivers and people living with schizophrenia, such as knowledge and skills, social support and coping, burden, family functioning, positive feelings, and psychological distress of caregivers, as well as symptoms, functioning, and recovery of people living with schizophrenia; (2) compare the total cost of the WIFI program plus the Reward Policy with the Reward Policy alone, including the program itself, health care utilization of people living with schizophrenia and family caregivers, and production loss of family caregivers; and (3) conduct a process evaluation of the WIFI program to assess fidelity and quality of program implementation, as well as user attitudes toward the program. To simultaneously assess intervention effectiveness and implementation strategies using mixed methods in “real-life” health care settings, we used a stepped-wedge cluster randomized trial (SWCRT) design [44].

## Methods

### Setting

The study will be conducted at Changsha Psychiatric Hospital (also named The Ninth Hospital of Changsha). Established in 1952 and affiliated to Changsha Civil Affairs Bureau, Changsha Psychiatric Hospital has the responsibility of prevention, treatment, and rehabilitation for all residents with mental illnesses in Changsha City. The hospital not only provides out-patient and in-patient health care, but also extends its services to community-based mental health care for its 12 affiliated communities, including the “686 Program” and Reward Policy implementation. The “686 Program” is China’s largest demonstration project in mental health service aimed at integrating hospital and community services for serious mental illnesses, with the following services provided mainly through community health workers: patient registration and initial assessment, free medication and regular follow-up in the community, management of community emergencies, and free emergency hospitalization [45-47]. In Changsha Psychiatric Hospital, a medical team involving three psychiatrists and four nurses is responsible for the “686 Program,” and the members circulate around the 12 communities each month to delivery free medicines to over 1000 registered clients who they know very well after long-term visits. The Reward Policy is a newly issued policy to encourage family care of people with serious mental illness, with RMB 200 (US $28.6) per month currently offered to each family registered under the 686 Program by Changsha Psychiatric Hospital.

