### Design

This study uses a pragmatic stepped-wedge design [44] to evaluate both the effectiveness and implementation strategy of the WIFI program. The CONSORT checklist is presented in Multimedia Appendix 1, and the SPIRIT checklist is presented in Multimedia Appendix 2. We will conduct a multicenter prospective controlled trial, using a stepped-wedge design, comparing the WIFI program integrated into the Reward Policy (intervention group) and the Reward Policy alone (control group) in family caregiving among people living with schizophrenia.

In a SWCRT, all clusters are randomly and sequentially crossed over from control to intervention over a number of time periods [48]. All clusters serve as a control group at the beginning of the study and end up in the intervention group at the end of the study. Compared with traditional randomized controlled trials and parallel cluster studies, a SWCRT enjoys unique ethical benefits since all clusters will ultimately receive the assumingly beneficial intervention at the end of the study [49]. In addition, a SWCRT enables analyses of any temporal effects of the intervention since each cluster acts as its own control and also allows for estimation of both between- and within-cluster effects of the intervention owing to repeated measurements [49]. As a result, a SWCRT design achieves greater statistical power with smaller sample sizes and is more cost-effective than parallel group designs.

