Participants of the study will include both people living with schizophrenia and their family members. The inclusion criteria for participating people living with schizophrenia are as follows: (1) registration in the “686 Program;” 2) fulfilling the Chinese Classification of Mental Disorders-3 (CCMD-3) or the International Classification of Diseases-10 (ICD-10) criteria for schizophrenia; (3) age 18 years or older; (4) living with at least one family member; and (5) ability to use a smartphone and WeChat to read and communicate. The inclusion criteria for participating family members are as follows: (1) registration in the Reward Policy and receiving a subsidy for family care; (2) living with a person having schizophrenia for at least the past 2 years; (3) age 18 years or older; 4) involvement with caregiving activities of people living with schizophrenia; (5) ability to use a smartphone and WeChat to read and communicate; and (6) at least one family member having a smartphone with the WeChat app installed.

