### Intervention

Participants in the control group will receive the usual financial benefits of the Reward Policy and receive payments from Changsha Psychiatric Hospital. However, they will not have access to the WIFI program since they cannot scan the WeChat barcode for the research.

Participants in the intervention group will receive the usual financial benefits of the Reward Policy as well as the WIFI program that will include the following three key components: psychoeducation through WOA publications, peer-support through a WeChat chat group, and professional support through WeChat private chat and video calls (Table 2).

**Table 2 table2:** Content of the WeChat-based integrative family intervention program.

Component	Format	Frequency	Leader	Possible content/topics
Psychoeducation	WeChat official account publications	Weekly	Psychiatrists and researchers	What is schizophrenia? What causes schizophrenia? How is schizophrenia treated? What can be done to promote recovery in schizophrenia? What are the early signs of relapse? What support do families need? How can feelings of stigma be addressed?
Peer support	WeChat chat group of people living with schizophrenia	Daily	People living with schizophrenia volunteers	Introduce self and tell your story; identify a specific problem encountered to discuss with the group; discuss skills and techniques used to cope with challenging situations; share feelings and resources; organize offline activities for support and stress reduction, such as hiking, dinner, and group meetings.
Peer support	WeChat chat group of caregivers	Daily	Caregiver volunteers	Introduce self and tell your story; identify a specific problem encountered to discuss with the group; discuss skills and techniques used to cope with challenging situations; share feelings and resources; organize offline activities for support and stress reduction, such as hiking, dinner, and group meetings.
Professional support	Private WeChat chat and video call	Monthly	Psychiatrists	Evaluate symptoms and function in people living with schizophrenia; update on medication and treatment; troubleshoot specific problems; provide consultation, guidance, assistance, etc.

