### Contamination

Since randomization is performed at the community level, using the stepped-wedge design, the risk of contamination between the control and intervention groups is very low. Moreover, since the intervention is delivered through WeChat and each participant scans the special WeChat barcode of the research program to obtain access to the WIFI program, it is unlikely that participants in the control group will receive the intervention during the control stage. Even if participants in the control group learn about the WeChat account of the research program, they will not be able to add it because the research team will recognize each participant and decline any request from the control group until receiving the allotted sequence to join the intervention. Thus, intervention contamination will be avoided.

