The study has some unique advantages and innovations. First, the WIFI program recruits the whole family of people living with schizophrenia as the intervention target, which may produce more far-reaching positive effects than interventions targeted at people living with schizophrenia alone or caregivers alone. In Asian countries like China, family cohesion and harmony are the core of the family-oriented culture. Interventions targeted at the family not only directly improve the well-being of each member, but also improve the family dynamic, which, in turn, will promote each member’s well-being. Second, the WIFI program is based on the most widely used social media platform in China (WeChat), which is accessible, affordable, feasible, and cost-effective. Compared with traditional on-site interventions, the WeChat-based intervention provides both synchronous and asynchronous communication that can serve a broad range of respondents who would otherwise not be recruited owing to time restraints and geographical constraints. Third, the WIFI program provides the most comprehensive intervention by integrating all three key components of family intervention that have been internationally recognized (psychoeducation, peer support, and private/professional support). Each component has its unique effect in improving the health outcome of people living with schizophrenia and their family members, and the components compensate each other to maximize the benefits to the family. Fourth, the stepped-wedge design has ethical advantages by ensuring all participants receive the intervention, as well as statistical advantages by generating more sound and robust scientific evidence than a traditional randomized cluster trial. Fifth, the WIFI program involves a medical team with both clinical psychiatrists and psychiatric nurses who work as both intervention implementers and data collectors. The medical team has a long close relationship with the community and is well accepted by people living with schizophrenia and their families, which can greatly increase the participant recruitment rate. In addition, the medical team knows about each person living with schizophrenia and can make more accurate assessments regarding the symptoms and functions of people living with schizophrenia, which can further increase the reliability and validity of the WIFI program.

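### The claim that contamination will be avoided does not cover the staff who implement WIFI and also visit communities still in their control periods, and the comparator should be described as including usual 686 Program care

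*Protocol article*

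**What the plan says.** **Comparator.** The Design section describes the trial as "comparing the WIFI program integrated into the Reward Policy (intervention group) and the Reward Policy alone (control group"). The Intervention section describes the control condition only in financial terms: "Participants in the control group will receive the usual financial benefits of the Reward Policy and receive payments from Changsha Psychiatric Hospital". The aims and Table 1 note d use the same label.

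**Background care.** Registration in the 686 Program is the first inclusion criterion for patients (Participants and Recruitment). The Setting section lists that program's services as including "free medication and regular follow-up in the community, management of community emergencies, and free emergency hospitalization". One hospital team of three psychiatrists and four nurses is responsible for it, and "the members circulate around the 12 communities each month to delivery free medicines to over 1000 registered clients".

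**Who delivers WIFI.** The Abstract says WIFI is implemented through the 686 medicine-delivery process. The Discussion says WIFI involves "a medical team with both clinical psychiatrists and psychiatric nurses who work as both intervention implementers and data collectors", and identifies this team by its long relationship with the communities. In Table 2, psychiatrists lead professional support and share the lead on psychoeducation with researchers.

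**Contamination.** The Contamination section cites randomization at community level and refusal of account access to control participants, and ends: "Thus, intervention contamination will be avoided". The Design section adds that communities are grouped partly by geographic distance.

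**The concern.** All three safeguards act on participants or on the distance between communities. None acts on a provider who works in every community. Randomizing communities cannot separate a team that visits all of them.

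From Step 1 onward, staff who have begun giving WIFI guidance in some communities keep making monthly visits to those still waiting. Advice, troubleshooting and teaching about schizophrenia can be given in person without any WeChat account. If some of this content reaches families still in control periods, the difference between conditions shrinks. The Statistical Analysis section takes time as a fixed effect, so a leak that begins with Step 1 would look like a general improvement over time. With no record of exposure, a diluted or null result could not be told apart from a program that does not work.

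A smaller point concerns description. The control label names only the subsidy, although every enrolled patient is also in the 686 Program. Readers need to know this for the cost comparison in the second aim and for judging where the result would carry over.

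**Working it through.** **1. Exposed control periods (Table 1: 12 communities, 5 periods, 4 groups of 3).**
- Baseline: 12 control community-periods, before WIFI has started anywhere.
- Step 1: 9 control. Step 2: 6. Step 3: 3. Step 4: 0.
- Total control: 12 + 9 + 6 + 3 = 30. WIFI: 60 - 30 = 30.
- Control while WIFI runs elsewhere: 9 + 6 + 3 = 18, and 18/30 = 60%.
- At one team visit a month and 2 months per period: 18 x 2 = 36 community visits by the shared team. The 12 baseline periods cannot be affected.

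**2. What the planned model would return.** Suppose those 18 periods receive a fraction f of the WIFI effect. The documents give no value for f, so it is an assumption. With the true effect scaled to 1, expected outcomes are 0 at baseline, f in the 18 exposed control periods, and 1 in WIFI periods. Fit outcome = period effect + theta x (WIFI indicator), with community effects. Take a period effect of 0 at baseline and f in Steps 1 to 4, with theta = 1 - f:
- baseline: 0 + 0 = 0;
- exposed control: f + 0 = f;
- WIFI: f + (1 - f) = 1.

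Every cell is fitted exactly, so the estimate is (1 - f) of the true effect and the leak sits in the period effects. A numerical check gave the same ratio with or without the baseline period, and with assumed within-person correlations of 0, 0.5 and 0.7.

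**3. Illustrative size.** The Power Analyses section plans on a ZBI change of 45 - 30 = 15 points. It states no standard deviation, so its sample size of 235 can be neither reproduced nor refuted; this point does not dispute it. Starting from its nominal 90% power and taking a two-sided 5% level (sidedness is not stated), power = Phi[(1 - f) x (1.960 + 1.282) - 1.960].

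| f (assumed) | Expected estimate if the true change is 15 | Power, nominal 90% |
|---|---|---|
| 0.1 | 15 x 0.9 = 13.5 | about 83% |
| 0.2 | 15 x 0.8 = 12 | about 74% |
| 0.3 | 15 x 0.7 = 10.5 | about 62% |

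These rows show what an assumed leak would do. They do not estimate how large any leak will be.

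**4. The comparator.** 686 registration applies to every patient in every period. Care common to both conditions cancels in the comparison, so omitting it from the label does not move the treatment estimate.

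**The case against.** **The route is narrow.** Official-account publications and peer chat groups need account access, and volunteers lead the peer groups. Professional support is a private WeChat contact led by psychiatrists; nurses are not listed as leaders. The Setting section says 686 services come mainly through community health workers, and team members visit to deliver medicines to over 1000 clients (about 1000/12 = 83 per community). This stands: any leak would be partial and mainly psychiatrist-led advice or teaching.

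**Some of that advice may be usual care.** The team has known these families for a long time. Guidance already given before Step 1 belongs to the comparator and causes no dilution. The documents do not show that staff behavior in control communities changes after Step 1. This also stands, and it is why the point is a risk.

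**Staff roles are not fully settled.** The Blinding section says the program team will not assess outcomes, whereas the Discussion calls the medical team both implementers and data collectors. That conflict concerns assessment. It does not remove the team's role as implementers.

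**The size is assumed.** Correct: (1 - f) follows directly from assuming the same f in all 18 periods. What the algebra adds is that the planned model would not reveal such a leak.

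**An article need not carry staff instructions.** That is fair for operational detail. But the article makes an unqualified claim, and the reasons it gives do not support it.

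**The comparator label.** A reader might infer that the label is wrong, or that the trial cannot support a conclusion against the Reward Policy. The documents do not bear this out. 686 care is disclosed under Setting and eligibility, the subsidy is offered to families registered in the 686 Program, and the intervention label omits 686 care too. The word alone can fairly be read as without WIFI.

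**Conclusion.** The point holds as a claim stated too strongly about a risk the design itself creates. The same team implements WIFI and visits all 12 communities monthly, including during 18 of the 30 control community-periods, and no stated safeguard addresses this. The likely direction is toward no effect. The size is unknown: the (1 - f) result rests on a uniform leak starting with Step 1, and a leak that varied by community or period need not follow that simple form.

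A reader might go further and infer that control periods will be contaminated, or that the trial's estimate is known to be diluted. Nothing in the documents shows this. The comparator wording is incomplete, not wrong. It bears on the cost comparison and on generalizability, and does not bias the within-trial contrast. The changes are worth making before Step 1, because exposure not recorded at the time is hard to recover later.

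**What to change.** 1. **Contamination section:** say that contamination is limited, not avoided, and name the shared-staff route.
2. **Same section:** state that WIFI materials and WIFI program content are not used at medicine-delivery visits in communities that have not yet crossed over, and that usual 686 care is unchanged.
3. **Data collection:** add one item on WIFI content received to the online questionnaires already completed in each period. Report the rate by period, for communities in control periods, beside the treatment effect.
4. **Aims, Design, Table 1 note d and Intervention:** describe the comparator as the Reward Policy plus usual 686 Program care.

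The cost is one extra questionnaire item at each assessment, a short staff instruction and some wording. The item is self-reported, and families may not always distinguish WIFI content from usual advice, so it would signal leakage without measuring it exactly.
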